### Purpose of the study

The purpose of the current study is to evaluate the efficacy of the newly developed UYB program in 10 Danish municipalities. More specifically, the aim of the study is to test whether Care As Usual (CAU) including the UYB program in comparison to CAU alone will lead to:Improved maternal competence (primary outcome)Improved paternal competence (secondary outcome)Improved parental mentalizing, i.e. reflective functioning and mind-mindedness (secondary outcome)Reduced parental stress (secondary outcome)Improved infant socioemotional development (secondary outcome)Reduced infant social withdrawal (secondary outcome)Reduced parental media use and infant screen time (secondary outcome)Increased information about infant socioemotional development (secondary outcome)Heterogeneity of effects across family types with more disadvantaged families and families met with more intensive UYB implementation gaining more from participation in the intervention (tertiary outcome)

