### Participants

#### Inclusion criteria

Parents living in one of the 10 municipalities participating in the project are invited to participate in the study. The parents have to be registered in the Danish Civil Registration Register (CPR) as parents to a newborn baby to be invited for the study. Mothers are invited if they are first-time mothers and if they are living on the same address as the child. Fathers/partners are invited if they have custody of the child or if they are living on the same address as the child, and they are invited regardless of whether they have children from previous relationships or not.

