### Background information and control variables

*Background information* about the parents is obtained as part of the 2- and 11-months questionnaire. At 2 months, this information includes questions about parental age, gender, ethnicity, educational background, employment status, income, relationship status, smoking, persons living in the household, the birth weight of the child, birth complications, and siblings to the child. At 11 months, parents are asked about breastfeeding, parental leave, and parental involvement with the child.

*Parental depressive symptoms* will be measured using the Edinburgh Postnatal Depression Scale (EPDS; [44]) or the Gotland Male Depression Scale (GMDS; [45]). The EPDS is a screening instrument for postnatal depression, which has primarily been validated in female samples. The EPDS contains 10 items assessing the presence of depressive symptoms in the past seven days (e.g. “I have felt sad and miserable”). Each item is rated on a four-point scale from “No, not at all” (= 0) to “Yes, quite a lot” (= 3). GMDS is a screening tool for male depression and consists of 13 items assessing whether the respondent’s behavior has changed during the last month (e.g. “More aggressive, outward-reacting, difficulties keeping self-control”). Each item is rated on a 4-point Likert type scale from “Not at all” (= 0) to “Extremely so” (= 4) [46]. For both questionnaires, items are summed to a total score with higher scores reflecting higher levels of depressive symptoms. These questionnaires are routinely given to parents typically around 8 weeks postpartum as part of the health visitors’ mental health screening program. The parents fill in the questionnaires during the health visitor’s visit in either a web-based or paper-and-pencil manner. The EPDS and GMDS data will be obtained from the health visitors’ register.

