### Statistical methods

The analyses of both primary and secondary outcomes will be conducted under the intention to treat principle where the participants are analysed according to their control CAU/intervention UYB status. However, as a secondary analysis, we will also conduct analyses where the actual intervention participation is taken into account (i.e. whether the families in the UYB group have been given the intervention by the health visitors). Thus, we will perform a contamination adjusted intention to treat analysis [61] which compliments the intention-to-treat approach by producing a better estimate of the effect of the UYB intervention.

The primary endpoint is PSOC at 11 months postpartum. The level of significance will be 5%, two-tailed [62]. The primary comparison of UYB and CAU interventions is analysed using linear mixed models with the health visitor as the second order variable. This is done to account for the correlation induced by the same health visitor conducting the CAU and UYB intervention for multiple families. We will control for maternal educational level in years, maternal level of depressive symptoms, and maternal age in years.

Secondary outcomes will be analysed in the same way as the primary outcome. Binary and categorical outcomes will be analysed with mixed logistic and multinomial logistic regressions, respectively, and continuous outcomes with mixed linear regression analyses. For outcomes where we are interested in the individual variance across time points, generalized estimating equations will be employed. All the analyses will be adjusted for the abovementioned covariates. As multiple tests will be conducted, we will both assess significance using the 5% significance level and adjust for multiple testing using the Bonferroni-Holm method [63].

For the tertiary outcome, we investigate whether some subpopulations benefit more from the UYB intervention. These subpopulations will be defined as disadvantaged families (e.g. based on background information such as employment status, income, etc.) versus advantageous families as well as families with a more intensive UYB implementation. In practice, we will test for significant subpopulations-group status interaction effects using linear moderation analyses (as otherwise described above).

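### The covariates fixed for every analysis are the mother's, so fathers' secondary outcomes are adjusted for the other parent's education, depressive symptoms and age rather than their own

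*Protocol article*

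**What the plan says.** All references are to the protocol article.

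- **Covariates (Statistical methods).** In the paragraph on the primary endpoint, maternal competence at 11 months: "We will control for maternal educational level in years, maternal level of depressive symptoms, and maternal age in years".
- **Other outcomes (same section).** "Secondary outcomes will be analysed in the same way as the primary outcome", and then "All the analyses will be adjusted for the abovementioned covariates". No other covariate set is listed, and no exception is made for fathers.
- **Fathers' outcomes (Purpose of the study).** The aims list "Improved paternal competence (secondary outcome" separately from the maternal primary outcome. Mentalizing, stress and media use are described there as parental outcomes, so they also cover fathers.
- **Data held on fathers (Background information and control variables).** "At 2 months, this information includes questions about parental age, gender, ethnicity, educational background, employment status". The same questionnaire asks about siblings of the child. For depressive symptoms, "GMDS is a screening tool for male depression and consists of 13 items"; the scores come from the health visitors' register.
- **Eligibility (Inclusion criteria).** Mothers must be first-time mothers. Of fathers and partners it says that "they are invited regardless of whether they have children from previous relationships or not".

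**The concern.** A covariate helps an outcome model in two ways: it explains outcome variance, and it removes a difference between the groups being compared. For a father's score, the natural candidates are his own mood, age, education and previous experience of parenting. The mother's values do either job only as far as they correlate with his.

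In a randomised trial this would be mainly a loss of precision. Here the usual-care families were recruited from May 2019 to February 2020 and the intervention families from February 2021 to February 2022, and the Discussion accepts that COVID-19 may have affected the groups differently. Covariate adjustment is therefore one of the few protections against differences in who enrolled in each phase. A shift in fathers' mood, age or education between phases would be only partly removed by the mother's values. Earlier children would not be captured at all: mothers are first-time by design, so prior parenting varies only among fathers and partners.

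There is also a practical cost. A father whose child's mother does not answer the 2-month questionnaire lacks her education. His record must then be imputed or dropped for want of a covariate that is not his.

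**Working it through.** **1. What the text fixes.** The covariates listed before the sentence that extends them to all analyses are maternal education, maternal depressive symptoms and maternal age. Nothing else is listed. The literal result for a paternal outcome is a model with three maternal covariates.

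**2. The plan's own figures.** The mismatch rests on no stated figure, but the sample size gives a scale. The recruitment target reproduces: 690 / (1 − 0.25) = 920. For the 690, the unadjusted two-sided formula at d = 0.2 and 80% power gives 393 per arm, 786 in total. The article used a simulation with three covariates and does not give their explained variance or the clustering variance. Ignoring clustering, 690 matches a covariate R² of 1 − 690/786 = 0.122. The 690 can be neither confirmed nor faulted.

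**3. Precision, depressive symptoms only.** The required sample is proportional to 1 − R², so the gain from own-parent adjustment is (1 − R² partner) / (1 − R² own). Assumptions, not in the documents: own symptoms correlate 0.3–0.5 with own score (R² 0.09–0.25), partner's symptoms 0.1–0.2 (R² 0.01–0.04).

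- Smallest gain: (1 − 0.04)/(1 − 0.09) = 0.96/0.91 = 1.05
- Middle values: (1 − 0.02)/(1 − 0.16) = 0.98/0.84 = 1.17
- Largest gain: (1 − 0.01)/(1 − 0.25) = 0.99/0.75 = 1.32

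Pairing low with low (0.99/0.91 = 1.09) and high with high (0.96/0.75 = 1.28) gives a narrower range, but nothing forces that pairing. The assumptions support 5–32%.

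**4. The same loss as power.** Assumptions: 345 fathers per arm, d = 0.2, no clustering, and partner covariates explaining r² × own R², with r the within-couple correlation (0 to 0.7). Power = Φ(0.2·√(345/2)/√(1 − R²) − 1.96).

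| Own R² | Power, own covariates | Power, partner's covariates |
|---|---|---|
| 0.122 | 0.80 | 0.75–0.77 |
| 0.20 | 0.84 | 0.75–0.79 |
| 0.30 | 0.88 | 0.75–0.81 |

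The loss is about 3–5 points at R² = 0.122 and up to about 13 points at 0.30.

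**5. Residual confounding.** Let the fathers' own covariate differ between phases by δF SD, the mothers' by δM SD, with coefficient b and couple correlation r. Adjusting for the mother's value leaves a bias of b(δF − r·δM); adjusting for the father's own value leaves none from that source. Assume δF = 0.2, b from −0.3 to −0.45, r from 0.2 to 0.5, and δM = 0 or 0.2.

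- Smallest: −0.3 × (0.2 − 0.5 × 0.2) = −0.03 SD
- Largest: −0.45 × (0.2 − 0) = −0.09 SD

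In absolute size this is 0.03/0.2 = 15% to 0.09/0.2 = 45% of the target effect.

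**6. Earlier children.** If fathers with previous children differ by 0.3 SD and their share shifts by 10 percentage points between phases, the bias is 0.3 × 0.10 = 0.03 SD. Both inputs are assumptions; the documents report no such shift.

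**The case against.** The strongest reply is that this is condensed wording and not a decision. The maternal covariates stand in the paragraph on a maternal outcome. Analysing other outcomes in the same way could mean using the matching parent's covariates. The male depression scale is presented as a control variable and would have little purpose otherwise, and father-specific coding is often left to the analysis plan. Part of this stands: the authors may well intend own-parent adjustment. But the text refers back to a list that is explicitly maternal and applies it to all analyses. An analysis plan that follows it literally would use the wrong parent's values.

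Several stronger readings are tempting and are not supported:

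- **That the fathers' data are never used.** The missing-data paragraph names education, parental age and depressive symptoms as possible predictors for imputation, and the tertiary analysis draws on background information to define subgroups. The gap is confined to adjustment of the outcome models.
- **That the primary result is compromised.** Maternal covariates suit maternal competence and are defensible for infant outcomes.
- **That the depression score is a post-exposure variable.** The article says "These questionnaires are routinely given to parents typically around 8 weeks postpartum". Table 2 puts the first ADBB observation, the setting for the intervention dialogue, at 2 months in six municipalities, 2–3 months in two and 4 months in two. The two events may coincide, but their order is not stated. This is a possibility only.
- **That Frederiksberg and Næstved form a clean pre-exposure subset because their first ADBB is at 4 months.** The video library has a section for 0–2 months, and the optional cards and social media are not tied to the ADBB. Parents there can meet the intervention earlier.
- **That a family random intercept is needed.** The article does not describe a model pooling both parents' reports.

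**Conclusion.** The point holds for the fathers' secondary outcomes. As written, the rule adjusts them for the wrong parent, in a design where adjustment has to deal with cohort differences as well as precision. The text alone establishes the mismatch.

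Its size depends on assumed correlations, phase differences and numbers of fathers. Within the ranges used above, the precision loss is modest to moderate, and the residual bias could be a meaningful fraction of a 0.2 SD effect. None of these figures predicts what the trial will find. The primary comparison is unaffected by the mismatch. The timing of the depression score is a separate and weaker matter that justifies at most a sensitivity analysis.

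**What to change.** Replace the blanket sentence with a rule by reporter:

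- Adjust each parent-reported outcome for the reporting parent's own age, education and depressive score (EPDS or GMDS), in separate models for mothers and for fathers/partners. The two scales should not enter one covariate unstandardised; state which scale applies to a partner for whom a male scale does not fit.
- For fathers/partners, add an indicator of previous children. The 2-month sibling question should supply it, provided it also captures half-siblings living elsewhere.
- Keep the maternal covariates for maternal and infant outcomes, and say so.
- Optionally, report the primary analysis also without the depression score, because that score may coincide with or follow first contact with the intervention.

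The change is to wording, and the variables are already planned for collection. The cost is some extra missing GMDS values, which the planned multiple imputation can handle. It should be settled before outcomes are compared by group.

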### The study interventions

During the project’s first phase, the participants will receive the existing publicly available postnatal care services (CAU) in the 10 municipalities and these may vary as described in Table 2. In the project’s second phase, the participants will receive the UYB intervention integrated into the existing publicly available postnatal care services in the 10 municipalities. The dose of UYB will therefore vary according to the variation in the existing postnatal care services (Table 2).

**Table 2 Tab2:** Information on visits from the health visitor and ADBB observations in the 10 municipalities

	Number of visits from the health visitor 0–12 months postpartum	Infant's age (months) when ADBB is conducted	Number of ADBB observations in total	ADBB observation 2–3 months	ADBB observation 4–6 months	ADBB observation 8–10 months
*Municipality*						
Aalborg	5	2, 4–6, 8–10	3	X	X	X
Frederiksberg	5	4, 8	2		X	X
Holbæk	6	2, 4, 8	3	X	X	X
Hvidovre	7	2, 8–10	2	X		X
Høje-Taastrup	6	2–3, 4–6	3	X	X	
Køge	5	2–3, 4–6, 9–10	3	X	X	X
Lolland	7	2, 4, 6, 8	4	X	X	X
Middelfart	6	2, 4, 8	3	X	X	X
Nyborg	5	2, 8–10	2	X		X
Næstved	7	4	1		X	

ADBB = Alarm Distress Baby Scale

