### The Understanding Your Baby intervention

In the study’s second phase, the experimental group of first time parents receives the UYB integrated into the existing publicly available postnatal care services, i.e. the amount of potential delivered UYB range from one to five in the 10 municipalities (see Table 2). The UYB is delivered by health visitors to all first-time parents during routine home visits.

The UYB is a universal educational parenting intervention aimed at supporting and promoting parents’ curiosity and knowledge about their infants’ socioemotional needs, ability to meet their infants’ needs, and thereby facilitating the development of a secure attachment and infant optimal socioemotional development. The UYB uses the routine ADBB observational situation as a standardized setting for a systematic sharing of knowledge and a dialogue with parents about their infants’ socioemotional cues, needs, and development in all families—i.e. this dialogue takes place in all cases—whether or not the ADBB observation gives rise to a concern regarding the infant’s socioemotional development. Although the primary purpose of the ADBB observation is early identification of persistent infant social withdrawal, the ADBB also provides an optimal context to guide caregivers about their child’s social and emotional development. During the interaction between the health visitor and the infant, the health visitor articulates specific infant behaviors and help the caregivers to interpret these behaviors in terms of mental states. For instance, when the infant looks away, the health visitor may explain to the parents that the infant needs a break to regulate themselves because interaction and eye contact is very stimulating for small children. In this way, the parents are shown their infant’s behavioral cues and how these behaviors are expressions of the inner world of the infant.

The UYB consists of four elements, each of which are described in the following: The UYB manual, the UYB dialogue cards, the UYB online video library, and UYB profiles on the social media platforms Facebook and Instagram.

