*Intensity of UYB implementation* will be measured as a combination of data obtained from the health visitors’ register and questions asked to the parents about the different UYB elements. The data obtained from the register will be the number of ADBB-screenings during the first year of life, and whether the health visitor was certified in UYB at the time of the screening. The questions asked to the parents include number of home visits during the first year of life, and whether they have seen the dialogue card(s), followed UYB on social media, or used the video library. The questions regarding the number of home visits, the dialogue card(s), and the social media will be asked at 11 months while the questions regarding the video library will be asked at 2, 4, 7, and 11 months.

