Parenting Sense of Competence Scale (PSOC)	X	X	X	X	
Parental Reflective Functioning Questionnaire (PRFQ)		X	X	X	
Parental Mind Mindedness (MM)—written description	X	X	X	X	
Parenting Stress Index, Fourth Edition—short form (PSI-4-SF)		X		X	
Ages and Stages Questionnaire®: Socio-Emotion, Second Edition (ASQ:SE-2)				X	
Alarm Distress Baby scale (ADBB)					X
Parental media use and infant screen time	X	X	X	X	
Information about infant development				X	
*Only UYB*					
Intensity of UYB implementation				X	

*CAU* Care As Usual. *UYB* Understanding Your Baby

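### UYB intensity is recorded only in the UYB group, so the planned interaction with group status cannot be estimated for it; only an exploratory within-UYB association is available

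*Protocol article*

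**What the plan says.** The tertiary aim under Purpose of the study includes the hypothesis of "families met with more intensive UYB implementation gaining more from participation in the intervention". Under Statistical methods, the subpopulations are disadvantaged families "versus advantageous families as well as families with a more intensive UYB implementation", and for all of them the article says "we will test for significant subpopulations-group status interaction effects using linear moderation analyses". It gives no other model for intensity.

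Table 3 (under Secondary study outcomes) places "Intensity of UYB implementation" in its last block, which is headed as applying to the UYB group alone. Background information and control variables describes intensity as a combination of two sources:

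- **Register:** "The data obtained from the register will be the number of ADBB-screenings during the first year of life", together with the visitor's UYB certification status at the screening.
- **Parents:** the number of home visits, and "whether they have seen the dialogue card(s), followed UYB on social media, or used the video library".

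Under Study design, health visitors are trained in UYB only once CAU data collection is finished.

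**The concern.** An interaction with group status asks whether the UYB–CAU difference changes with the level of a family characteristic. That needs the characteristic to be defined, and to vary, in both groups. Disadvantage meets this condition. Intensity of UYB implementation does not, because CAU families precede the training and the variable is not collected for them.

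At stake is what may be concluded. What the data can yield is a comparison of UYB families with one another. If that were read as moderation, a link between engagement and outcome would stand in for evidence that stronger delivery produces a larger effect. Part of the composite is parents' own behaviour after they enter the study: they decide whether to watch the videos or follow the social media profiles. Families with high intensity may therefore differ in motivation from the rest.

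**Working it through.** The article states no figure for this test, so there is none to reproduce. The question is whether the model can be estimated.

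**Inputs.** Group G (0 = CAU, 1 = UYB), moderator M, and three covariates (maternal education, depressive symptoms and age; Statistical methods). The fixed part of the model is

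Y = b0 + b1·G + b2·M + b3·G·M + three covariate terms,

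which has 7 columns. The health-visitor random effect does not change the rank of these columns.

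**Case 1: intensity coded 0 in CAU.** When G = 0, M = 0 and G·M = 0. When G = 1, G·M = M. So G·M = M for every family, two columns are identical, and the rank is 7 − 1 = 6. Only the sum b2 + b3 is determined, never b3 alone. A high/low coding of intensity gives the same result.

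**Case 2: intensity missing in CAU, complete cases used.** Only UYB families remain. G equals the intercept column and G·M again equals M, so the rank is 7 − 2 = 5.

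**Numerical check.** The matrices were built on simulated data with 690 families (the article's analysed sample size), an equal split (assumed) and intensity scored 1 to 5 (assumed). The aliasing follows from the coding and does not depend on these choices.

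| Model | Columns | Rank |
|---|---|---|
| G, M, G·M; intensity 0 in CAU (continuous or high/low) | 7 | 6 |
| G, M, G·M; intensity missing in CAU | 7 | 5 |
| G, M only; intensity 0 in CAU | 6 | 6 |
| G, M, G·M; disadvantage, both groups | 7 | 7 |
| G, M, G·M; ADBB count, both groups | 7 | 7 |

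**What the third row estimates.** The coefficient of M is the slope among UYB families. Comparing high- and low-intensity UYB families each with all of CAU does not help, because the CAU mean cancels:

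(mean high − mean CAU) − (mean low − mean CAU) = mean high − mean low.

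The result is a contrast within UYB, in which intensity was not assigned.

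**Which components occur where.**

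| Component | Occurs in CAU? | Settled mainly by |
|---|---|---|
| Number of ADBB screenings | yes | municipality schedule and visitor; visits are voluntary |
| Number of home visits | yes | municipality schedule; visits are voluntary |
| Visitor certified in UYB | no | training programme |
| Dialogue card(s) seen | no | visitor (one card mandatory, three optional) |
| Video library used | no | parent, once informed |
| UYB followed on social media | no | parent |

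**The case against.** The strongest reply is that intensity is not wholly foreign to CAU. ADBB screenings and home visits take place in both phases, ADBB register data are listed for both groups in Table 3, and the coding of CAU as 0 is not stated in the article. A moderator built from these two counts could be crossed with group (rank 7 of 7). This stands, and it rules out saying that no component of intensity exists in CAU. It does not rescue the planned test. Such a moderator measures how intensive usual care is, not the composite that the article names and records for UYB only.

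A second reply is that dropping the redundant column leaves a model that can be fitted. That is also true. The defect is therefore in the label and the interpretation, and it is too strong to say that nothing can be learned about intensity. How a later paper would word the result cannot be known from the article.

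The contamination-adjusted analysis does not fill the gap. It concerns whether families were given the intervention, not whether more intensive delivery brings more benefit.

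A reader might also infer support from Table 2. Its totals run from 1 to 4, whereas the text says "the amount of potential delivered UYB range from one to five in the 10 municipalities" and refers to that table. Høje-Taastrup shows two age windows and two marks against a total of 3. The first is awkward and should be reconciled. The second is ambiguous, since three observations could fall in two windows: Lolland has four listed ages and three marks. Neither bears on whether the interaction can be estimated.

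**Conclusion.** The point holds in a narrow form. As stated, the interaction test cannot be estimated for intensity: it is aliased with the intensity main effect if CAU is coded 0, and group is constant if CAU is missing. What remains is a within-UYB slope, which does not show that the UYB–CAU difference varies and is open to self-selection.

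This rests on intensity being the UYB-only variable of Table 3 and on CAU families having no planned UYB exposure. The Discussion has CAU data collection running to September 2020, while training began in August 2020 (Dates defining periods of recruitment and follow-up). A few late CAU families might have had some contact with trained visitors, but intensity is not recorded for them, so the conclusion does not change.

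A reader might infer that the whole tertiary outcome, or the trial's main result, is compromised. The article does not support that. Intensity is one of two kinds of moderator in a tertiary outcome, the disadvantage interaction is estimable, and the primary analysis is untouched. Severity is moderate to low.

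**What to change.** 1. Keep the group-status interaction test for disadvantage only.
2. Replace the intensity test with a dose-response model within the UYB group, labelled exploratory and associational. Report the delivery components (ADBB screenings done, certified visitor, mandatory dialogue card) separately from parent-chosen video and social-media use. Note that even the ADBB count depends partly on families, because visits are voluntary. State that intensity is not applicable in CAU, so that it is not treated as missing and imputed there.
3. Optionally, add group by scheduled number of ADBB observations per municipality (Table 2, "Number of ADBB observations in total") as a further exploratory analysis. It is defined in both phases and not chosen by the family. State its limits: it measures the usual-care schedule, it rests on 10 municipalities, and it removes only period effects common to all of them. Three municipalities had delayed training and later birth cohorts, so period effects specific to a municipality would remain. Check the Table 2 totals against the listed ages and the text before using them.

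Items 1 and 2 cost wording only and need no new data. Their price is a weaker claim: an association within UYB in place of evidence that the intervention effect grows with intensity. Item 3 adds one analysis, probably of low power.

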### Primary study outcome

*Parenting competence* will be measured using the Parenting Sense of Competence Scale (PSOC; [47, 48]). In the current study, the Danish version of the PSOC translated by Lange et al. [49] is used. The most commonly used tool for measuring parental competence is the PSOC [50]. The PSOC was originally developed by Gibaud-Wallston in 1977, and the scale has subsequently been revised and used in a number of studies (for instance, [51–53]). The PSOC consists of 17 items rated on a 6-point Likert type scale from “Strongly agree” to “Strongly disagree”. The scale has two subscales, with eight of the items being summed together to calculate the Skill/Knowledge subscale and the remaining nine items being summed together to create the Valuing/Comfort subscale. A total score is calculated by summing all 17 items (of which nine are reverse-scored), with higher scores indicating a higher level of parenting competence [54]. Parenting competence is measured at 2, 4, 7, and 11 months.

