### Sample size

We used the R package simr [59] to conduct a power analysis. We wanted to be able to detect a small effect size (Cohen’s *d* = 0.2; [60]) using a linear mixed model with one predictor (i.e. group status) and three covariates (all continuous). Using a power of 0.80 and a significance level of 0.05, 690 participants are needed in order to detect a small effect. Assuming that 25% of the participants drop out after intake and before the endpoint, a total of 920 participants will have to be recruited. A participant is considered to have dropped out when they actively withdraws from the study or does not answer any of the questionnaires.

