Regarding missing data, the first step will be to delete the group status variable to be blinded. If more than 95% of the observations are complete, a complete case analysis will be conducted. Otherwise, data-driven, pragmatic choices will be made in selecting a few background variables (e.g. educational level, parental age at birth, level of depressive symptoms) to see which ones are strong predictors of missing status and then use multiple imputation to handle missing data [64]. Imputations will be conducted using the software package ‘mice’ [65].

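### The missing-data steps delete group status first and never restore it before imputation; followed in that order, they pull the UYB–CAU difference toward zero.

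*Protocol article*

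**What the plan says.** The missing-data paragraph closing Statistical methods sets out a sequence:

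1. "the first step will be to delete the group status variable to be blinded".
2. "If more than 95% of the observations are complete, a complete case analysis will be conducted".
3. Otherwise a small set of background characteristics is examined "to see which ones are strong predictors of missing status and then use multiple imputation to handle missing data". The examples given are education, parental age and depressive symptoms.
4. The imputation is run in the R package mice.

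No step says when group status comes back. The same section makes the comparison of UYB with CAU on PSOC at 11 months the primary analysis, in a linear mixed model with three maternal covariates. Sample size targets d = 0.2 with 80% power, needs 690 participants, and recruits 920 on this basis: "Assuming that 25% of the participants drop out after intake and before the endpoint". Under Primary study outcome, "Parenting competence is measured at 2, 4, 7, and 11 months".

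**The concern.** An imputation model should contain every variable in the analysis model, above all the one being tested. If group is absent, a missing UYB score and a missing CAU score with the same covariates are drawn from the same distribution. Imputed values then carry almost none of the group difference and dilute the difference among the observed mothers. This happens even when data are missing completely at random, where a complete-case analysis would be unbiased. The health visitor cannot stand in for group, because the article says the same health visitors serve both groups.

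The trial is built to detect a small effect. The Discussion argues that even a small benefit matters, and that inferiority to CAU would point to possible harm. Dilution works against both aims. The tertiary tests of interaction with group status are exposed in the same way.

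**Working it through.** **Inputs from the protocol article.** d = 0.2, two-sided 5%, 80% power, 690 analysed, 25% dropout, 920 recruited (Sample size, Statistical methods); about 1,130 infants expected (Abstract).

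**Assumptions, not in the article.** Equal groups, outcome missing completely at random, no health-visitor clustering, 20 imputations combined by Rubin's rules, covariate R² about 0.12.

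**Reproducing the plan's figures.** 690 / (1 − 0.25) = 920, as stated. Without covariates, d = 0.2 needs 393 per group, 786 in all. The stated 690 follows if the covariates explain 1 − 690/786 = 0.122 of the variance, hence R² of about 0.12.

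**Group omitted, background covariates only.** Let m be the missing share and U = 4(1 − R²)/N, with M = 20.

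- Expected estimate: d(1 − m).
- True variance of the estimate: about (1 − m)U + mU/M.
- Variance reported by Rubin's rules: about U + (1 + 1/M)mU.

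For N = 920 and m = 0.25:

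- U = 4 × 0.88/920 = 0.003826.
- Estimate: 0.2 × 0.75 = 0.15.
- True SD: √(0.002870 + 0.000048) = 0.0540.
- Reported SE: √(0.003826 + 0.001004) = 0.0695.
- Power: Φ[(0.15 − 1.96 × 0.0695)/0.0540] = Φ(0.26) = 0.60.

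**Group included.** Power is close to that of complete cases: SE = √(0.003826/0.75) = 0.0714, and Φ(0.2/0.0714 − 1.96) = Φ(0.84) = 0.80.

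**Power, formula / simulation:**

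| N | Missing | Estimate without group | Power without group | Power with group |
|---|---|---|---|---|
| 920 | 10% | 0.18 | 0.81 / 0.81 | 0.87 / 0.86 |
| 920 | 25% | 0.15 | 0.60 / 0.61 | 0.80 / 0.79 |
| 920 | 40% | 0.12 | 0.31 / 0.32 | 0.71 / 0.73 |
| 1,130 | 10% | 0.18 | 0.89 / 0.87 | 0.925 / 0.91 |
| 1,130 | 25% | 0.15 | 0.71 / 0.71 | 0.87 / 0.87 |
| 1,130 | 40% | 0.12 | 0.41 / 0.40 | 0.79 / 0.76 |

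The simulated powers carry Monte Carlo error of a few points. Separate runs at 40% missing and N = 920 with group included gave 0.66 to 0.73. With 20% missing in CAU and 30% in UYB, the simulated estimate is again 0.149.

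**No true effect, 25% missing.** The estimate is centred on zero. The test rejects too rarely: 1.96 × 0.0695/0.0540 = 2.52, a type I error of about 0.01 (about 0.02 in simulation).

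**An earlier PSOC score in the model, group still omitted.** If that score has residual correlation r with the 11-month score and carries the same effect, the estimate is about d[(1 − m) + mr]. With r = 0.6 and m = 0.25 this is 0.2 × (0.75 + 0.15) = 0.18. With r = 0.7 it is 0.185 (simulated 0.186).

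**The case against.** A reader might infer that the protocol commits to imputing without group. It does not say so outright. The deletion is given a purpose, blinding, and the judgement-laden steps that blinding would protect follow at once. The primary analysis needs group, so it must return at some point. Returning it after the variables are chosen and before mice is run is a possible reading. What stands is that deletion is the stated first step, imputation follows in the same sequence, and nothing reverses the deletion in between. An analyst working down the list would impute without group.

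A reader might also take 25% as the plan's forecast of missing 11-month PSOC. The article defines a dropout as someone who actively withdraws or answers no questionnaire at all. A mother who answers at 2 months but not at 11 is not a dropout, yet lacks the endpoint. Someone who never answered has no questionnaire-based education or age from which to impute. The imputed share could therefore lie below or above 25%, which is why a range is shown; 40% is only an illustration.

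A third tempting reading is that leaving out earlier PSOC and the health-visitor level is itself an error. The background variables are introduced as examples, and the full imputation model is detail that a condensed article may leave to the analysis plan. The loss would also be smaller if earlier scores entered.

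Finally, the error cannot manufacture a benefit, and it can be repaired before analysis. Both points are correct. They limit the harm but do not remove it.

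**Conclusion.** The point holds as a defect in the stated order of steps. The bias is toward zero, by up to about the fraction imputed: roughly 10%, 25% and 40% of the effect at those levels of missingness when only background variables are used. At 25% missing, the simulated loss of power is about 18 points with 920 mothers (0.79 to 0.61) and about 16 points with 1,130 (0.87 to 0.71).

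These figures rest on the assumed missingness mechanism, R² and absence of clustering, and on the literal reading of the sequence. If group is in fact restored before imputation, the bias disappears and only the wording needs repair. Reaching more than 95% completeness is unlikely given the dropout allowance, so imputation will probably be used for the primary comparison and the ambiguity should be settled beforehand.

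**What to change.** State that group status is removed only while the auxiliary variables are chosen. State that it is then restored before imputation, under a coded label if blinding is to continue. Include group in every imputation model together with the analysis covariates, or impute separately by group. Separate imputation also serves the tertiary interaction tests; with a single model, the relevant interactions should be added.

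As an optional gain, use the PSOC scores from 2, 4 and 7 months as predictors, since they are already collected. The primary analysis model does not need to change.

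The cost is a revised paragraph and a few lines of mice code, with no new data and no effect on recruitment or follow-up.
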